#### **(4) Safety Observation**

- During cardiorespiratory exercise tests, if any of the following danger signs appear before the patient reaches symptomatic limits, consider terminating exercise: central nervous system symptoms like dizziness, vertigo, etc. If blood pressure decreases instead of increasing during exercise, dropping more than 20mmHg from

baseline systolic blood pressure. Pathological Q waves or severe arrhythmias on electrocardiogram, such as multiple frequent ventricular arrhythmias. Severe hypertensive response (e.g., systolic blood pressure  $\geq 220$ mmHg).

- During the 6MWT, consider stopping the test if any of the following danger signs appear: suspected angina with chest pain; intolerable shortness of breath; leg spasms or extreme leg muscle fatigue; gait imbalance; pallor, sweating; dizziness or fainting; SpO2 consistently below 85%; systolic blood pressure drops  $\geq 20$ mmHg with an increased heart rate; systolic blood pressure  $\geq 180$ mmHg or diastolic blood pressure  $\geq 100$ mmHg; inability of the participant to continue the test.
- During moxibustion treatment, observe and record any allergic reactions or burn injuries that occur during or after treatment.

### **(5) Trial Evaluation Indicators**

- Concomitant Medications: Record the medications taken by participants during the trial, especially those that may influence the study results, such as beta-blockers.
- Dropout and Exclusion Rate Assessment: Detailed statistics on the number, time, assessment status, and reasons for dropout or exclusion during the trial, along with calculation of dropout and exclusion rates.
- Compliance Evaluation: Record the actual number of times participants received moxibustion treatment during the trial. Calculate the ratio of actual treatment received to planned treatment, for compliance assessment.

### **(6) Observational Time Points**

- After participants are enrolled, collect basic information (general information, dietary habits, exercise habits, etc.) and baseline measures, including VO2peak, AT, serum CCB, 6MWD, SF-36, and QBSQ;
- After the 4th and 8th weeks of treatment, conduct and record twice interim assessments, including VO2peak, AT, serum CCB, 6MWD, SF-36, and QBSQ;
- At the end of the treatment (12 weeks), collect basic information again (general information, dietary habits, exercise levels, etc.) and outcome indicators, including VO2peak, AT, serum CCB, 6MWD, SF-36, and QBSQ;
- Follow-up until the 24th week, evaluating indicators including VO2peak, AT, 6MWD, SF-36, and QBSQ.

-----

## **7. Observation of Adverse Events**

### **(1) Definition**

The term "adverse event" encompasses any symptom, syndrome, or disease occurring in patients during clinical research that affects patient health. This also includes clinically relevant situations identified in the laboratory or other diagnostic procedures, requiring unplanned diagnostic or therapeutic measures, resulting in withdrawal from

the study, or showing clinically significant abnormal laboratory test results.

Adverse events may be new diseases; worsening of symptoms or signs related to the treatment status or the disease itself; unrelated to participation in the trial; or a combination of one or more factors. Therefore, the term "adverse event" does not necessarily imply a causal relationship with the trial therapy.

A serious adverse event refers to adverse events occurring at any dose of the study treatment regimen or at any time during the observation period, including those resulting in death; immediate life-threatening situations; hospitalization or prolonged hospital stay; permanent or severe disabilities; overdose-related events; causing cancer; congenital abnormalities; of significant medical importance (referring to events that do not immediately endanger life or cause death or require hospitalization but may harm patients or require measures to prevent one of the defined consequences); requiring medical intervention to prevent permanent damage or harm.

#### (2) Expected Adverse Reactions in the Trial

Although preclinical data has not shown adverse reactions, attention should still be paid to potential local blisters, itching, and rash reactions.

#### (3) Causality Assessment of Adverse Events with Drugs

According to the standards set by the National Center for Adverse Drug Reaction Monitoring of the Ministry of Health (see "Guidelines for Clinical Research of New Traditional Chinese Medicine (Trial)"), an assessment of the possible relationship between adverse events and investigational drugs is made using a five-level classification system: "certain, probable, possible, suspected, unlikely." Assessment criteria can be found in the "Adverse Event Form" in the study medical records.

#### (4) Management of Adverse Events

- **Observation and Recording:** Investigators should request patients to truthfully report changes in their condition after drug administration and avoid leading questions. Any adverse reactions occurring during the trial should be recorded on the "Adverse Event Form," and investigations should be conducted, detailing the process and results of handling until laboratory tests return to normal and symptoms disappear. The follow-up method can vary from hospitalization, outpatient visits, home visits, phone calls, correspondence, etc.
- **Medical Care:** When adverse reactions are discovered, investigators decide on diagnosis and treatment measures based on the condition, and determine whether to discontinue observation. In the case of serious adverse events, the unit conducting the clinical research must take necessary measures immediately to ensure the safety of participants.
- **Reporting:** Investigators complete the "Serious Adverse Event Report Form" and report to the department, medical office, and ethics committee within 24 hours, signing and indicating the date on the report.

-----  
**8. Assessment Criteria for Efficacy and Safety**

(1) Comprehensive Efficacy Assessment Criteria: Statistical differences in the main outcome indicators are used to judge efficacy.

(2) Criteria for Severity of Adverse Events:

- Mild: Tolerable for participants, does not affect treatment, requires no special treatment, and has no impact on participants' recovery.
- Moderate: Difficult for participants to tolerate, requires withdrawal of drugs to stop the trial or special treatment, and has a direct impact on the participants' recovery.
- Severe: Endangers the participants' lives, causes death or disability, requires immediate drug withdrawal, or urgent treatment.

-----  

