## Abstract

**Title:** "Clinical protocol quantification and optimization study of moxibustion to improve cardiorespiratory endurance in the elderly"

**Objective:** To observe the clinical effects of moxibustion in improving cardiorespiratory fitness in apparently healthy older adults; to apply and promote the clinical protocol of moxibustion for tonifying Qi and blood, improving cardiorespiratory fitness in older adults, effectively assisting older adults in maintaining health, improving quality of life, and contributing to elderly care.

**Study Design:** Randomized controlled trial.

**Participants:** Older adults from neighboring communities of the second affiliated hospital of Nanjing University of Chinese Medicine, Jianye District, Nanjing, China.

**Sample Size:** A total of 105 participants for the study on the clinical effects of moxibustion in improving cardiorespiratory fitness, with 35 participants in the moxibustion group, sham moxibustion group, and blank control group, respectively.

**Treatment Protocol:** (1) Moxibustion group: Moxibustion on bilateral Zusanli (ST36), Shenque (CV8), and Guanyuan (CV4) acupoints, 60 minutes per acupoint, once daily, five times a week (with weekends off), for a total of 12 weeks; (2) Sham moxibustion group: Utilization of specially modified moxibustion device to isolate the heat and radiation of moxa burning. Acupoint selection, moxibustion time, and frequency are the same as the moxibustion group; (3) Blank control group: No interventions given.

**Inclusion Criteria:** (1) Age between 60-80 years old. (2) Normal cognition and ability to complete all assessments and treatments. (3) CPET test indicating impaired cardiorespiratory fitness ( $VO_{2peak} < 20\text{ml}\cdot\text{kg}^{-1}\cdot\text{min}^{-1}$  or  $6\text{MWD} \leq 450$  meters).

**Primary Outcome Measures:** (1) Peak Oxygen Uptake ( $VO_{2peak}$ ), (2) Anaerobic Threshold (AT), and (3) serum central carbon metabolites (CCB), including thirty-four CCB-related biomarkers such as adenosine triphosphate (ATP), nicotinamide adenine dinucleotide ( $\text{NAD}^+$ ), pyruvic acid, and acetyl-coenzyme A (Acetyl-CoA).

**Secondary Outcome Measures:** (1) 6-minute walk distance (6MWD), (2) the Short Form 36 Health Survey (SF-36), and the Qi and Blood Status Questionnaire (QBSQ).

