## **2. Research Objectives**

The primary goal is to apply and promote the clinical protocol of moxibustion for tonifying Qi and Blood, thereby enhancing cardiorespiratory fitness in elderly individuals. The aim is to effectively assist the elderly in maintaining health, improving their quality of life, and contributing to elderly care initiatives. This study intends to observe the variations in primary outcome indicators ( $VO_{2peak}$ , AT value, serum central carbon metabolites, 6MWD, etc.) and adverse events occurring under the intervention of moxibustion. It aims to evaluate its effectiveness and safety.

-----

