The specific testing procedure includes: ① Resting phase (3 minutes): Obtain resting heart rate, blood pressure, electrocardiogram, static gas metabolism, and other indicators; ② Unloaded warm-up exercise phase (3 minutes): Maintain a cycling speed of 55-65 r/min, record heart rate, blood pressure, electrocardiogram, blood oxygen saturation, etc., close to the end; ③ Power load phase (6-10 minutes): Maintain cycling speed at 55-65 r/min, closely observe participant's symptoms, heart rate, blood pressure, gas metabolism indicators, blood oxygen saturation, and changes in the electrocardiogram. Note potential adverse reactions during the test, such as angina, breathing difficulties, dizziness, paleness, sweating, significant rapid or slow arrhythmias, ischemic changes in the electrocardiogram, blood pressure drop, shock, etc. If any of these symptoms or signs appear during exercise, the test should be immediately terminated, and appropriate observation and treatment should be given; ④ Recovery phase (6-8 minutes): Maintain slow cycling without load for 2-3 minutes, cycling speed can be maintained at 30-40 r/min, observe the participant's heart rate, blood pressure, electrocardiogram, and symptoms. Stop cycling without load, and continue observing whether the participant's vital signs such as heart rate and blood pressure return to pre-test levels. If symptoms and/or abnormal signs persist for more than 15 minutes after terminating exercise, further observation or treatment is required.

• **Primary Outcome Measures: Serum Central Carbon Metabolites (CCB)**

The main steps of the detection process include sample collection, target metabolite extraction, standard curve establishment, LC-MS/MS detection, and data analysis.

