① Instrumentation used: AB Sciex QTRAP® 6500+ Mass Spectrometer, AB Sciex Exion LC™ Liquid Chromatography. ② Reagents: 34 central carbon-related substance standards and 5 stable isotope-labeled standards purchased from Shanghai Zhenzhun Biotechnology Co., Ltd.; Methanol, Acetonitrile, Formic acid, Ammonium acetate (LC-MS, Thermo-Fisher, USA), Aminomethanediphosphonic acid (Sigma-Aldrich, USA), Milli-Q ultrapure water (Millipore, USA). ③ Sample collection: Participants fasted and venous blood was collected in the hospital laboratory. Blood was allowed to clot at room temperature in a centrifuge tube or vacuum blood collection tube for 1 hour. Then centrifuged at 3000rpm for 10 minutes, the supernatant was transferred into 1.5mL centrifuge tubes (0.2mL per tube). After labeling, samples were rapidly frozen in liquid nitrogen for 15 minutes and stored at -80°C. ④ Preparation of standard solutions: Accurately weighed 34 central carbon-related substance standards to prepare a mixed standard solution with a concentration of 100μg/mL. Methanol was used to dilute the

linear mother liquor to obtain working solutions of various concentrations. Solutions of D-Glucose-13C6, (s)-Malicacid-D3, Succinic acid-D4, dAMP lithium salt-15N5, and D-Glucose-6-phosphate disodium salt-13C6 were prepared at certain concentrations and mixed to obtain an internal standard solution (IS). Mother liquor and working solutions for linearity, internal standards, and quality control were stored at -20°C.

Metabolite extraction: Take 100mg of sample and add 500µL of mixed internal standard solution (methanol: water = 4:1). Mix well, stand for 5 minutes, centrifuge at 12000rpm for 10 minutes, and take the supernatant for LC-MS analysis. ⑤ Chromatographic and mass spectrometric methods: Chromatographic column: Waters Atlantis Premier BEH Z-HILIC (2.1×100mm, 1.7µm); Mobile phase: Phase A: 15mM Ammonium acetate + 10µm Aminomethanediphosphonic acid aqueous solution; Phase B: 15mM Ammonium acetate/Acetonitrile; Column temperature: 50°C; Injection volume: 2µL; Flow rate: 0.4 mL/min. Mass spectrometry conditions: Electrospray ionization (ESI), negative ionization mode. Ion source temperature at 550°C, ion source voltage at -4500V, curtain gas at 35psi, and both nebulizer gas and auxiliary gas at 60psi. Multiple reaction monitoring (MRM) was used for scanning.

- **Secondary Outcome Measures: Six-Minute Walk Test (6MWT)**

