### (2) Statistical Analysis Methods

Summarize the demographic characteristics of each group and baseline variable measurements. The Kolmogorov-Smirnov test will be used for assessing data normality. Continuous data will be represented as the mean  $\pm$  standard deviation for normally

distributed data and median (range) for non-normally distributed data. Paired t-tests or analysis of variance (ANOVA) will be used to assess changes in primary and secondary outcomes before and after intervention. Analysis of variance or Kruskal-Wallis test will be used for pairwise comparison of primary and secondary outcomes among groups. Chi-square or Fisher's exact test will be used for analyzing categorical data. Pearson or Spearman correlation analysis will be used to assess the correlation between variables. Statistical analysis will be conducted using the Windows version of the Social Sciences Statistics Software Package (SPSS) 27.0, with significance set at a two-tailed P-value of  $<0.05$ . Graphical analysis will be performed using GraphPad Prism software (version 9.4.0).

-----

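### The efficacy criterion in Section 8(1) rests on 36 primary measures and two controls with no hierarchy, deciding contrast or designated primary visit, so it permits an efficacy claim with uncontrolled error

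*Protocol*

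**What the plan says.** - **Criterion.** Section 8(1): "Statistical differences in the main outcome indicators are used to judge efficacy". It names no measure, control or visit, and does not say whether one or all must differ.
- **Primary measures.** The Abstract lists VO2peak, AT and "serum central carbon metabolites (CCB), including thirty-four CCB-related biomarkers such as adenosine triphosphate (ATP" and others. Section 6(4) repeats VO2peak and AT as primary and adds "Primary Outcome Measures: Serum Central Carbon Metabolites (CCB".
- **6MWD.** Section 2 places it among the primary indicators ("AT value, serum central carbon metabolites, 6MWD, etc.) and adverse events occurring under the intervention of moxibustion"). The Abstract and Section 6(4) make it secondary ("Secondary Outcome Measures: Six-Minute Walk Test (6MWT").
- **Tests.** Section 11(2) plans before/after tests within groups and ANOVA or Kruskal-Wallis for pairwise comparison among the three groups, "with significance set at a two-tailed P-value of" below 0.05. It states no adjustment.
- **Visits.** Section 6(6): "After the 4th and 8th weeks of treatment, conduct and record twice interim assessments". It ties outcome indicators to the end of treatment at 12 weeks and lists week 24 as follow-up. VO2peak and AT are measured at weeks 4, 8, 12 and 24; the metabolites are listed at weeks 4, 8 and 12 only.
- **Sample size.** Section 3 is built on one two-group comparison of VO2peak: difference 2.6, SD 3.0, 5% level, 90% power.

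**The concern.** A decision criterion should tell the reader, before the data are seen, which result counts as success. This one refers to a list of 36 variables and two comparators and leaves the rest open. Whether one or all measures must differ, which control decides and which visit counts could all be settled after unblinding without departing from the protocol.

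Two consequences follow. A shift in one metabolite, or a difference from untreated participants that sham moxibustion would also have shown, could be reported as evidence that moxibustion improves cardiorespiratory fitness. And a nominally significant result could not be read at its face value of 5%, because the set of tests that could have produced it is not bounded. Section 2 widens that set by adding 6MWD and ending the list with an open-ended term.

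**Working it through.** **1. The plan's own figure.** Inputs from Section 3: difference 2.6, SD 3.0, two-sided 5%, 90% power, 15% dropout. The standardised difference is 2.6/3.0 = 0.867. A two-sample t-test needs 28.97, so 29 per group. 29/(1 - 0.15) = 34.1, so 35 per group and 3 x 35 = 105. The stated 29, 35 and 105 are reproduced. They belong to one measure, one control and one test.

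**2. Number of tests the criterion could cover.**
- Primary measures: 2 + 34 = 36 (37 with 6MWD).
- Two controls, one visit: 36 x 2 = 72.
- Two controls, all listed post-baseline visits: (2 x 4 + 34 x 3) x 2 = 220.

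**3. Chance of at least one P < 0.05 with no true effect, if one difference suffices and tests are independent.**
- 36 tests: 1 - 0.95^36 = 84.2%.
- 72 tests, treated as independent: 1 - 0.95^72 = 97.5%. Allowing for the shared moxibustion arm gives about 97%.

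**4. Allowing for correlation.** The protocol gives no correlations between measures, so a range is assumed. Simulation of 36 equally correlated null measures in three equal arms at one visit, two-sided 5% per test (29 per arm for the last two columns):

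| Correlation between measures | vs sham | vs sham or blank | vs sham or blank, only if overall ANOVA is significant |
|---|---|---|---|
| 0 | 84% | 97% | 78% |
| 0.5 | 55% | 78% | 52% |
| 0.7 | 36% | 57% | 35% |
| 0.9 | 18% | 31% | 17% |

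**5. VO2peak and AT alone.** Against two controls at one visit: about 12-17% without the ANOVA step and about 5-9% with it. Most of the excess therefore comes from the metabolites.

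**6. Several visits.** Counting every listed visit against both controls, without the ANOVA step and with between-visit correlation 0.5 to 0.8, gives 95-98% at inter-measure correlation 0.5, 81-90% at 0.7 and 52-64% at 0.9.

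**7. Cost of adjusting instead of choosing.** By the normal approximation (which gives 28 for the single test at 5%), Bonferroni over two controls for VO2peak needs 34 evaluable per arm, 40 with dropout. Over 72 tests it needs 59, or 70 with dropout, and power at 29 per arm falls to 46%. A single primary test keeps 29 and 35.

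**The case against.** A reader might infer that Section 8(1) declares efficacy on any one significant difference. It does not say so. The plural wording sets neither one nor all, and a rule requiring all measures to differ would not inflate the error. That objection stands, and the percentages above are conditional on the one-difference reading. It does not rescue the criterion. An all-measures rule would demand significance on 34 metabolites in a trial sized for VO2peak only, and leaving the choice open allows it to be made after the results are known.

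A reader might also infer four interchangeable visits. The documents do not support that: the metabolites are not listed at week 24, weeks 4 and 8 are called interim, and outcome indicators are tied to week 12. Week 12 is implied but not designated primary. The main table assumes a single visit, so it does not depend on this point.

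The ANOVA named in Section 11(2) may be meant as a gate before pairwise tests. For three groups this restrains the error within one measure, and it brings VO2peak and AT close to nominal. It does nothing across 36 measures: 17-78% remains.

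The figures also count differences in either direction. Counting only those favouring moxibustion, one visit against either control without the ANOVA step gives about 15-81% over the same correlations.

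Finally, multiplicity adjustment is commonly left to the SAP, which is not shown, and silence in Section 11(2) does not prove that none is planned. But the efficacy criterion, the list of primary measures and the conflict over 6MWD are fixed in the protocol. An SAP would have to override them, so the correction belongs here.

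**Conclusion.** The point holds as a defect in a stated decision criterion. Thirty-six primary measures and two controls stand behind it, with no hierarchy, no deciding contrast and no formally designated primary visit.

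Under the one-difference reading, the single-visit false-positive chance is above 5% in every 36-measure case examined: about 18-84% against sham, 31-97% against either control, and 17-78% against either control with an ANOVA gate. Counting several visits raises it further. These ranges rest on assumed equal correlations from 0.9 down to 0 and on no true effect on any measure.

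Whether a false claim is more likely than not depends on correlations that the protocol does not give, so that stronger statement is not supported across the whole range. The sample size is correct for its own single comparison but makes no allowance for the rest. This should be corrected before analysis.

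**What to change.** - Replace Section 8(1) with one primary test: VO2peak at week 12, the end-of-treatment outcome visit, moxibustion against sham, two-sided 5%. This matches the single VO2peak comparison behind the sample size.
- If it is significant, test in this order, each at 5%, stopping at the first failure: VO2peak against blank, AT against sham, AT against blank.
- Make the 34 metabolites secondary, with false discovery rate control.
- Label weeks 4, 8 and 24 secondary for all measures.
- Remove 6MWD and the open-ended term from the primary list in Section 2.

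The choice of sham as the deciding control and the order of the sequence are design decisions for the sponsor. What matters is that they are fixed before the data are seen.

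**Cost.** The changes are to wording in the protocol, carried into any SAP, with no added participants. AT or metabolite results alone could no longer support an efficacy claim. Section 3 does not say which control the pilot difference of 2.6 (SD 3.0) came from. The sponsor should state this, because the 90% power applies only to that comparison. If the pilot control was untreated, power against sham is not established by the figures given.

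### The adverse-event severity grades leave a gap between Mild and Moderate and overlap between Moderate and Severe, which makes severity counts unreliable, especially against the blank arm

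*Protocol*

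**What the plan says.** Protocol section 8(2), Criteria for Severity of Adverse Events, sets three grades:

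- **Mild** covers events described as "Tolerable for participants, does not affect treatment, requires no special treatment"; recovery must also be unaffected.
- **Moderate** covers events described as "Difficult for participants to tolerate, requires withdrawal of drugs to stop the trial or special treatment"; recovery must also be directly affected.
- **Severe** covers an event that threatens life, or that "causes death or disability, requires immediate drug withdrawal, or urgent treatment".

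Mild and Moderate are lists closed by *and*. Severe is a list closed by *or*.

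Section 7(2), Expected Adverse Reactions, says that "attention should still be paid to potential local blisters, itching, and rash reactions". The Safety Observation part of section 6 adds allergic reactions and burns during or after moxibustion.

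Section 5 describes a moxibustion device, a sham device and a blank control group that gets no treatment. No arm receives a study drug.

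On causality, section 7(1) accepts that an adverse event may be "unrelated to participation in the trial". Section 7(3) fixes five levels: "certain, probable, possible, suspected, unlikely".

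Section 2 names safety beside effectiveness as what the trial sets out to evaluate. Section 11(1) lists a safety analysis without detail.

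**The concern.** A severity scale should place every event in exactly one grade, and should do so in the same way in every arm. This one looks as if it fails in three ways.

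- **Gap.** Mild excludes any event that requires special treatment. Moderate excludes any event that is well tolerated. An event with both features falls between them, and the local skin reactions that the protocol tells staff to watch for can have both.
- **Overlap.** A need for withdrawal appears in Moderate, and a need for immediate withdrawal appears in Severe. One event can satisfy both definitions.
- **Mixed criteria.** Intensity, the action judged necessary and the effect on recovery are combined in one grade. Withdrawal of a drug has no meaning in the blank arm, and recovery is an awkward criterion for participants whom section 3 describes as apparently healthy.

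What is at stake is the safety description. Staff facing an event that fits no grade or two grades must improvise, and two of them may do so differently. Grades are assigned when events occur, so a later analysis plan cannot fully repair them.

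**Working it through.** The plan gives no figure on this point, so there is none to reproduce. The check is a logical one: translate the three definitions into yes/no conditions and see which combinations each grade accepts.

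**Inputs (all from section 8(2)).** Six attributes of an event:

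- T: tolerable
- W: treatment affected or withdrawal required
- S: special treatment required
- R: impact on recovery
- U: immediate withdrawal or urgent treatment required
- L: threat to life, death or disability

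**Rules.**

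- Mild = T, and none of W, S, R. It is also taken to exclude U and L, which the text does not spell out.
- Moderate = not T, and (W or S), and R.
- Severe, any-one reading = L or U. Severe, joint reading = L and U.

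**Number of combinations.** Six yes/no attributes give 2^6 = 64. A need for immediate withdrawal or urgent treatment implies W or S, so the 2^3 = 8 combinations with U but neither W nor S drop out: 64 − 8 = 56.

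| Reading of Severe | No grade | One grade | Two grades | Total |
|---|---|---|---|---|
| Any one condition suffices | 12 | 35 | 9 | 56 |
| Both conditions needed | 34 | 19 | 3 | 56 |

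A gap and an overlap exist under either reading. Every double grade is Moderate with Severe.

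**The gap.** Take the events that are neither urgent nor life-threatening: 2^4 = 16 combinations of T, W, S and R. One is Mild. Three are Moderate (not T, R, and W only, S only, or both). The remaining 16 − 1 − 3 = 12 have no grade. One of the 12 is T with S alone: a tolerable blister, burn or rash that requires special treatment. It fails Mild on S and Moderate on T.

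**The overlap.** Take a poorly tolerated event that affects recovery and requires immediate withdrawal, without threat to life. It meets all three Moderate conditions. It meets Severe on the any-one reading, which is the natural one for a list closed by *or*. On the joint reading this event would be Moderate only, and the overlap moves to events that are also life-threatening or disabling. No rule says that the higher grade prevails.

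**How wide the overlap is among events with withdrawal.** With W present there are 2^5 = 32 combinations. Both grades need not T and R, with S free (2 options) and at least one of U and L (3 options): 2 × 3 = 6 of 32 on the any-one reading.

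**The blank arm.** W cannot occur. Of the 2^3 = 8 combinations left that are neither urgent nor life-threatening, 1 is Mild, 1 is Moderate and 6 have no grade. Only one of the three non-urgent routes to Moderate is open: hard to tolerate, special treatment, impact on recovery. The immediate-withdrawal route to Severe is closed as well; urgent treatment, threat to life, death and disability remain.

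All of these count logical combinations. They say nothing about how often events of each kind will occur.

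**Causality.** Set side by side, section 7(1) allows for events that have nothing to do with the trial, while the lowest level in section 7(3) is *unlikely*. The protocol does not say whether that level takes in unrelated events.

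**The case against.** The strongest reply is that this is a wording defect with narrow reach. Much of that reply stands, and it rules out several stronger readings.

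- **Comparison across arms.** A reader might infer that severity counts cannot be compared at all. The documents do not support that. Moxibustion and sham share the same criteria, and treatment can be stopped in both. Only the blank arm lacks the withdrawal route, and it keeps the special-treatment and urgent-treatment routes. Section 11(1) specifies no between-arm comparison of severity counts.
- **Every withdrawal double-graded.** A reader might infer this from the shared word. Moderate has further joint conditions and Severe asks for immediate withdrawal, so the overlap is narrow.
- **Grade set by action taken.** The text speaks of what an event requires, so the grade follows a judged need and not simply what was done.
- **All expected reactions ungradable.** Tolerable itching or rash that needs no treatment and affects neither treatment nor recovery is plainly Mild. Whether a simple dressing is special treatment is undefined, and the protocol does not say how often blisters need care.
- **Effect on who completes.** Section 4(3) removes participants for severe events when a physician judges that termination is necessary. It does not cite the section 8 grade, so feedback from grading into dropout is not shown.
- **Causality.** Section 7(3) refers to criteria on a form that is not shown, which may settle what the lowest level covers. One cannot say that blank-arm events must be tied to a treatment, or that all 105 participants are affected.

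It is also fair that section 7(4) already has the handling of events recorded, that section 7(1) defines seriousness separately, and that section 9(3) requires training for consistent quantification. None of this closes the gap or the overlap: training cannot give consistent grades from categories that omit some events and double-count others.

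**Conclusion.** The point holds in limited form. The section 8(2) grades are neither exhaustive nor mutually exclusive. A tolerable event that requires special treatment has no grade, and that is possible for the blisters, rash and burns that the protocol names. A poorly tolerated event that affects recovery and requires immediate withdrawal has two grades, with no rule to choose between them. Mixing intensity with judged action, in drug-trial wording, makes severity counts unreliable, especially against the blank arm.

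The effect on event counts cannot be put as a rate, because the protocol gives no expected frequencies. The conclusion rests on reading the conjunctions literally. The gap holds under both readings of Severe. An overlap also holds under both, but the particular example of immediate withdrawal without threat to life needs the any-one reading.

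This should be corrected because safety is a stated aim and the remedy is cheap. No efficacy conclusion or sample-size figure depends on it. The causality mismatch is a minor point for reconciliation.

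**What to change.** Rewrite section 8(2) as three mutually exclusive and exhaustive grades based on intensity, meaning discomfort and interference with daily activity, worded so that they apply to all three arms. Remove the drug-withdrawal and recovery wording from the grades. Record the action taken or required as a separate item on the Adverse Event Form. Leave seriousness to the definition in section 7(1).

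In section 7(3), either add an unrelated level or state that the lowest level includes unrelated events, so that it agrees with section 7(1).

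Which events lead to stopping treatment is a separate matter for the investigators to reconcile; this change does not touch it.

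Cost: about one paragraph of protocol text, a small form revision and brief retraining of the staff who grade events.
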